## Abstract

**Background:**

Xanthohumol (XN), a bioactive flavonoid from *Humulus lupulus* with anti-inflammatory properties, has potential benefits for patients with Crohn’s disease (CD), a type of inflammatory bowel disease. We recently completed and published results of a placebo-controlled phase I clinical trial demonstrating the safety and tolerability of 24 mg XN daily for 8 weeks. The present study aims to evaluate the safety and tolerability of the same dose of XN adults with clinically active CD in a placebo-controlled phase II clinical trial. Additional aims will assess the impact of XN on inflammatory biomarkers, platelet function, CD clinical activity, and stool microbial composition. The metabolism of XN will also be evaluated. This article provides a model protocol for consideration in investigations of XN or other natural products in disease states.

**Methods:**

A triple-masked, randomized, placebo-controlled trial will be conducted in adults with clinically active CD. Participants (*n* ≤ 32) will be randomized to either 24 mg encapsulated XN per day or placebo and followed for 8 weeks. Throughout the trial, participants will be queried for adverse events. Biomarkers of clinical safety, blood and stool markers of inflammation, platelet function, Crohn’s Disease Activity Index score, stool microbial composition, and XN metabolite profiles in blood, urine, and stool will be assessed every 2 weeks.

**Discussion:**

We describe the protocol for a phase II clinical trial that evaluates the safety and tolerability of XN in adults with active CD, as well as evaluate metabolism and mechanisms that are relevant to CD and other diseases with underlying inflammation and/or gut permeability. The effects of XN on inflammatory biomarkers, platelet function, the microbiota, and multi-omics biomarkers measured in this phase II trial of adults with CD will be compared to the effects of XN in healthy adults in our previous phase I trial. The results of the study will advance the evidence guiding the use of XN in patients with CD.

**Trial registration:**

ClinialTrials.gov NCT04590508. Registered on October 19, 2020

## Administrative information

Note: the numbers in curly brackets in this protocol refer to SPIRIT checklist item numbers. The order of the items has been modified to group similar items.

## Introduction

### Background and rationale {6a}

Phased investigations of the safety, tolerability, and efficacy of natural products have posed unique challenges in the drug development model over the last decades [1, 2]. Stakeholders including the National Center for Complementary and Integrative Health (NCCIH) identify these investigations as a top priority in the coming years [3]. The aim of this article is to provide a protocol for a placebo-controlled phase II clinical trial investigating the safety and tolerability of a natural product in adults with Crohn’s disease (CD).

Xanthohumol (XN), derived from resins of the female cones of the hops plant (*Humulus lupulus*), is a potential natural drug early in the development pipeline. XN has demonstrated anti-inflammatory and antioxidant activity in vitro and in vivo [4, 5], prebiotic effects on the gut microbiome and the metabolome in vivo [6, 7], and upstream regulatory effects on gene expression, specifically on nuclear erythroid 2-related factor 2 (Nrf2), nuclear factor-κ B (NFκB), and the farnesoid-X receptor (FXR) [8–13]. Together, these mechanisms of action have the potential to broadly benefit patients with a variety of conditions, particularly those with excessive inflammation and/or elevated intestinal permeability. This is especially true in patients with CD, where measurements of circulating inflammatory cytokines, clinical activity indices such as the Crohn’s Disease Activity Index (CDAI), hematologic markers of organ function, and monitoring of adverse events throughout the interventional period are minimum requirements to meet recommendations for a comprehensive assessment of safety and tolerability, while also providing early surrogate indicators of potential efficacy [14].

Our recent phase I clinical trial demonstrated the safety and tolerability of 24 mg/day of XN over 8 weeks in healthy adults [15], corroborated by previous animal and human pharmacokinetics models indicating XN is safe to consume as an isolated constituent [16–19]. Furthermore, the US Food and Drug Administration (FDA) classifies both hops and hops oil as “Generally Recognized as Safe” (GRAS) [20]. To date, recurrent daily administration of XN has not yet been evaluated for safety or tolerability in a population with acute or chronic disease. Due to its documented in vitro and in vivo mechanisms related to inflammatory conditions like CD, it is desirable to determine the potential of XN as a natural drug candidate [4–13].

To further this goal, this protocol reports the design of a phase II trial in participants with clinically active CD. Upon enrollment, up to 32 participants will be randomized to take 24 mg XN encapsulated with a rice protein vehicle, or an encapsulated rice protein placebo, daily for 8 weeks. Hematologic biomarkers of safety, CDAI scores, inflammatory biomarkers, platelet function, gut microbiome composition, and XN metabolite profiles in plasma, urine, and stool will be monitored every 2 weeks to evaluate the safety and tolerability of XN in CD and provide a comparison in metabolism against samples previously collected in healthy adults.

### Objectives {7}

The main objective of the phase II trial is to determine the safety and tolerability of 24 mg/day of orally delivered XN compared to a placebo over 8 weeks in a group of adults with active CD. Secondary objectives of this study include assessing the impact of XN on the clinical activity of CD, inflammatory biomarkers that are often elevated in patients with CD, the composition of the gut microbiome in patients with CD compared to healthy adults, and the hemostatic function of platelets, as well as measuring the metabolic pathways and metabolite concentrations of XN. A summary of objectives and outcomes can be found in Table 1.

**Table 1 Tab1:** Objectives and outcomes

Objectives Assessment of:	Measures	Method of assessment
*1. Safety and tolerability*	i. RBC, WBC, platelets ii. eGFR, electrolytes, BUN:Cr, AST, ALT, GGT, alkaline phosphatase, bilirubin iii. Heart rate, blood pressure, temperature, body mass index (BMI) iv. Adverse events and quality of life	i. Complete blood count (CBC) ii. Comprehensive metabolic panel (CMP) iii. Vital sign measurement iv. Adverse event monitoring and PROMIS-29 questionnaire
*2. Disease activity*	i. Clinical activity	i. Crohn’s Disease Activity Index (CDAI)
*3. Inflammation*	i. Inflammatory cytokines ii. Fecal calprotectin	i. Serum or plasma analysis ii. Fecal analysis
*4. Gut permeability and endotoxemia*	i. CD14, lipopolysaccharide (LPS) and LPS-binding protein, intestinal fatty acid binding protein	i. Plasma analysis
*5. Platelet function*	i. Platelet signaling, secretion, and procoagulant activity	i. Proteomic analysis ii. Flow cytometry
*6. Microbiome and bile acid compositions*	i. Metagenomic DNA sequencing and taxonomic profiling ii. Proteomic characterization iv. Bile acid profiling	i. Stool analysis ii. Activity-based proteomic assay iii. Plasma analysis
*7*. *Metabolic profile of XN*	iv. Xanthohumol (XN), isoxanthohumol, 6-prenylnaringenin, 8-prenylnaringenin, desmethylxanthohumol (DXN), dihydro-desmethylxanthohumol (DDXN)	iv. 24-h urinalysis, plasma analysis, stool analyses

#### Hypotheses

We hypothesize 24 mg/day of XN will be safe and tolerable in an adult population with active CD over an 8-week period. This will be supported by observing no greater than a 50% greater frequency in differences of laboratory abnormalities or adverse events in the XN group. We also hypothesize XN will improve the clinical activity and reduce inflammatory biomarker concentrations in CD, demonstrate a metabolite profile different than that of healthy adults, and generate a specific gut microbiome signature. These comparisons will be achieved by measuring data against that from the phase I clinical trial of the same interventional product and period.

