### Trial design {8}

This study is a phase II, triple-blind, 1:1 drug:placebo allocation, parallel-arm, randomized, placebo-controlled trial under an investigational new drug (IND) application to the US FDA. The trial is registered with ClinicalTrials.gov (NCT04590508).

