### Sample size {14}

A sample size of at least 12 participants per group provides 80% power to detect ≥50% difference in the proportions of participants experiencing laboratory abnormalities or adverse events at a threshold of *α* = .05 by *χ*^2^ test. This sample size, at *n* = 12 per arm, provides >90% power using 2-sided *t*-tests to detect a mean change of 0.25–0.5pg/mL in TNF-α in the treatment arm according to preliminary data from previous pilot studies. Accounting for attrition up to 25%, we will randomize up to 32 participants. Attrition during the phase I trial was 10% [15].

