## Statistical methods

### Statistical method outcomes {20a}

Laboratory measures will be analyzed first with descriptive statistics including mean, median, and standard deviation. Distributions will be tested for skew and transformed (e.g., natural log) as needed to reduce skew on subsequent analyses. If distributions indicate substantial non-normality that cannot be modified with transformation, non-parametric tests (e.g., Wilcoxon rank-sum) will be used.

In addition, the frequency of new, clinically significant laboratory abnormal values as outlined above will be monitored by the DSMB. The percentage of these new abnormal values per reference ranges will be reported at each time point and compared between groups by Fisher’s exact test. Assessment for changes in the distribution of each parameter will be presented as means and confidence intervals (CI) within and between groups. The significance of differences will be compared using 2-sided, unpaired *t*-tests if normally distributed and a non-parametric Wilcoxon rank-sum test of mean values between groups if non-normally distributed. Overall increases and decreases in laboratory parameters will be tested using linear mixed ANOVA with time point as a repeated factor, potentially suggestive of cumulative toxicity if trending in a clinically deleterious direction. All factors will be considered significant if *p* < .05.

Clinical activity will be measured through the CDAI. A score >150 is considered *clinically active* and is an eligibility criterion. Changes in score from baseline between groups will be compared within groups using two-sided, unpaired *t*-tests at each interval with the primary outcome as a change in value from baseline to closeout, whereas within-group changes will be compared using two-sided, paired *t*-tests. Non-parametric Wilcoxon rank-sum test of mean values between groups will be used if data are non-normally distributed.

Measures within the PROMIS-29 v.2.0 questionnaire include seven validated subscales, i.e., physical function, anxiety, depression, pain intensity, pain interference, sleep disturbance, and social interaction. Analyses will be performed by calculating descriptive statistics of mean, median, and mode of reported *T*-scores and overall PROMIS-29 questionnaire and each subscale. Welch’s *t*-test will be used to test the differences in scores between groups with *p* < .05 considered significant.

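### The 50% safety benchmark is an observed-value rule of unclear scale with no confidence limit, and at 12 to 16 per arm it cannot carry the safety conclusion

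*Protocol article*

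**What the plan says.** Objectives {7} makes safety and tolerability over 8 weeks the main objective. The Hypotheses section then says this will be supported by "observing no greater than a 50% greater frequency in differences of laboratory abnormalities or adverse events in the XN group". No confidence limit, test or error rate is attached to that sentence.

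Sample size {14} uses the same 50% figure: "A sample size of at least 12 participants per group provides 80% power" to detect a "≥50% difference in the proportions of participants" with laboratory abnormalities or adverse events, by a chi-square test at 0.05. It gives no placebo event rate and does not say whether the 50% is absolute or relative. It continues: "Accounting for attrition up to 25%, we will randomize up to 32 participants". Trial design {8} specifies "1:1 drug:placebo allocation".

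For new abnormal laboratory values, Statistical method outcomes {20a} says: "The percentage of these new abnormal values per reference ranges will be reported at each time point and compared between groups by" Fisher's exact test. The same section plans confidence intervals for the means of laboratory parameters. Neither is linked to the 50% benchmark.

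**The concern.** Two things look wrong. First, the hypothesis and the sample size share a number but seem to use different scales. A frequency up to half as high again is a ratio of 1.5, while a 50% difference in proportions, as sized, is 50 percentage points. At a 20% placebo rate the limits are 30% and 70% on XN.

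Second, on either scale the benchmark is met or missed by the observed frequencies alone. With about a dozen participants per arm these vary widely by chance.

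This is the only numerical threshold the article gives for the main objective, so a report could quote it as met. Background and rationale {6a} says repeated daily XN has not yet been evaluated for safety in people with acute or chronic disease. False reassurance would therefore matter.

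**Working it through.** **Inputs.** From Sample size {14}: 12 per arm, 80% power, alpha 0.05, a 50% difference, 25% attrition, up to 32 randomized. From Trial design {8}: 1:1 allocation. The placebo event rate is not given, so it is an assumption here, with 5% to 50% shown. The chi-square test is taken as two-sided, since its sidedness is not stated.

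**Step 1: reproduce the sample size on the absolute scale.** With pooled variance and no continuity correction,

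n per arm = [1.96·√(2p̄(1−p̄)) + 0.842·√(p₁(1−p₁)+p₂(1−p₂))]² / (p₂−p₁)².

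For 5% against 55%, p̄ = 0.30 and n = (1.270 + 0.457)² / 0.25 = 11.9, so 12 per arm, with power 80.2%. Then 24/(1−0.25) = 32. Both stated figures reproduce. At less favourable rates n is slightly larger: 14 for 10% against 60%, and 15 for 25% against 75% (power with 12 per arm: 76% and 71%). A one-sided test gives 12 for 20% against 70%.

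**Step 2: try a ratio of 1.5.** The same formula gives:

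| Placebo rate | n per arm for 80% power | Power with 12 per arm |
|---|---|---|
| 10% | 686 | 5.5% |
| 20% | 294 | 8.0% |
| 30% | 163 | 11.2% |
| 40% | 97 | 15.9% |
| 50% | 58 | 23.6% |

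Even at 66% against 99% it needs 20 per arm (16 one-sided). So 12 per arm does not come from a relative 50%.

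**Step 3: benchmark read as a ratio.** It is met when XN events ≤ 1.5 × placebo events. The probability is the sum of the products of the two binomial probabilities over all outcomes that qualify. With 12 per arm:

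| Placebo rate | True ratio 1: fails | True ratio 1.5: passes | True ratio 2: passes |
|---|---|---|---|
| 5% | 29% | 59% | 49% |
| 10% | 34% | 53% | 41% |
| 20% | 29% | 53% | 35% |
| 30% | 24% | 53% | 29% |
| 40% | 20% | 53% | 23% |
| 50% | 15% | 53% | 19% |

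If all 32 are retained (16 per arm) and the placebo rate is 20%, a doubling passes 33% of the time and a harmless product fails 26%. As an illustration, 4/12 on placebo and 6/12 on XN just meets the benchmark (ratio 1.5), yet its 95% interval on the log-ratio scale is 0.56 to 4.00.

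**Step 4: benchmark read as absolute.** It is met when (XN events − placebo events)/12 ≤ 0.5. From a 20% placebo rate, true excesses of 30, 40 and 50 points pass 91%, 78% and 58% of the time. Over placebo rates of 5% to 50% the ranges are 90–95%, 77–82% and 58–61%.

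**Step 5: precision available.** The approximate 95% half-width for a difference with the same rate p in both arms is 1.96·√(2p(1−p)/n). At p = 10% it is 24 points (n = 12) or 21 (n = 16). At 25% it is 35 or 30. At 50% it is 40 or 35. The range is therefore 21 to 40 points.

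**The case against.** The best reply is that the Hypotheses sentence is garbled, not contradictory. It uses the same 50% and speaks of differences, so it may mean the absolute threshold of the sample-size section. That cannot be excluded, and the absolute scale of the sample size is itself inferred from arithmetic, not stated. A reader might therefore infer a definite clash of scales, but the text supports only an ambiguity. Step 4 shows that the absolute reading removes the clash and makes the benchmark more lenient.

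A reader might also infer that the protocol treats a non-significant test as proof of safety. It does not say so anywhere. Fisher's test is planned as a comparison and no more. It would not fill the gap either: with 12 per arm its power against a doubling from 20% to 40% is about 9%.

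Nor does the whole safety conclusion rest on one sentence. The Hypotheses section says supported, not declared. Outcomes {12} builds a profile from laboratory changes, vital signs and adverse events. Section {20a} gives intervals for laboratory means, and Adverse event reporting and harms {22} adds severity, duration and case-by-case attribution. These stand.

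Finally, it would be too strong to say that almost any toxicity passes. On the absolute reading 20% against 80% passes only 34% of the time. The halting rule in section {11b}, at more than 20% of all participants, would also be crossed with probability about 99% at 20% against 60%, if every event met its criteria. Milder events would not count towards it.

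The ratio rule does discriminate somewhat at high placebo rates: at 50%, a harmless product passes 85% of the time and a doubling 19%.

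**Conclusion.** The point holds in this form: the 50% benchmark is a point-estimate rule of unclear scale, and on neither reading can it carry a safety conclusion with 12 to 16 per arm. At an assumed 20% placebo rate and 12 per arm, the error rates on the ratio reading are 35% (a doubling accepted) and 29% (a harmless product failed). On the absolute reading a 40-point excess is accepted 78% of the time. All of these depend on a placebo rate the article does not give, but the conclusion is the same across 5% to 50%. They also assume one yes/no outcome per participant and independent arms.

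The sample size is not at fault: 12 per arm and 32 in total follow from an absolute difference of about 50 points. What needs correcting is the criterion and its link to that calculation.

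**What to change.** 1. In Hypotheses and in Sample size {14}, state that the 50% is an absolute difference in the proportion of participants with at least one qualifying event.
2. Replace the observed-value criterion with the XN-minus-placebo difference in that proportion and its exact 95% confidence interval. Describe safety by the largest excess that the upper limit excludes.
3. State the expected precision as a range over assumed event rates: an approximate half-width of 21 to 40 points for 12 to 16 per arm at rates of 10% to 50%. A single figure such as 30 to 35 points would hold only near a 25% rate, and exact limits will differ somewhat from this approximation.

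This changes wording and adds one interval to the analysis. It needs no further participants or data, and the other safety summaries and the halting rule stay as written. The price is a more modest safety claim.

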The primary endpoint for laboratory values and vital sign measurements will be mean change from baseline to week 8, with changes also compared between groups from baseline to each additional follow-up visit (i.e., 2, 4, and 6 weeks). The frequency of new-onset or worsening laboratory values will be reported within groups throughout the trial at each biweekly visit. AEs and event severity will be reported as new-onset or worsening events spontaneously and at each biweekly visit. Together, these outcomes will provide a profile of safety and tolerability of 24mg XN for 8 weeks compared to placebo.

Secondary and exploratory outcomes include clinical disease activity, systemic inflammation (e.g., IL-10), intestinal permeability (e.g., intestinal fatty acid binding protein) and endotoxemia (e.g., LPS), platelet function, stool microbiome and bile acid composition, and the metabolic profile of XN in humans over 8 weeks. Each measurement will be collected at every biweekly clinical visit and compared between groups as mean change from baseline within groups and compared between groups at each follow-up visit. The primary endpoint for each secondary and exploratory outcome will be considered exploratory and reported as mean change within groups at week 8 from to baseline and compared between groups at each follow-up visit. The measurements to support these outcomes are outlined in Table 1.

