As this study will have a relatively small sample size, changes in secondary and tertiary outcome values will be considered preliminary but will be compared to results found in the phase I trial. Assessments for these outcomes, including inflammatory cytokines, gut permeability biomarkers, markers of endotoxemia, bile acids, and platelet function, will be calculated using Cohen’s *d* statistic for effect size and qualitatively compared for differences between trials using changes in values between baseline and closeout. The primary effect estimate will be for changes between baseline and closeout. This study is powered to detect a difference in Cohen’s *d* value of at least 1.2 between groups. Results will be considered evidence of a possible effect if a Cohen’s *d* value > 0.5 is observed. Statistical comparisons for significance will be considered exploratory and will be limited to unpaired *t*-tests between XN treatment groups.

The metabolite profiles and impact of XN on gut microbial composition and platelet function will be conducted with specific methods previously described by partner sites [31, 33]. Correlations between changes in CDAI and microbiota changes, inflammatory biomarker changes, and/or bile acid changes will be considered exploratory.

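### The protocol does not fix XN versus randomised placebo as the deciding contrast for its secondary efficacy outcomes, and its sections contradict one another on the comparator

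*Protocol article*

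**What the plan says.** Five parts of the protocol article bear on the comparator.

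- **Trial design {8}** describes a "1:1 drug:placebo allocation, parallel-arm, randomized, placebo-controlled trial", so a concurrent randomised control exists.
- **Hypotheses** puts efficacy and metabolism in one sentence: "We also hypothesize XN will improve the clinical activity and reduce inflammatory biomarker concentrations in CD, demonstrate a metabolite profile different than that of healthy". That sentence, cut short here, ends with a microbiome signature. The next sentence names the comparator for all of them: "These comparisons will be achieved by measuring data against that from the phase I clinical trial of the same interventional product and period". Placebo is not mentioned for these hypotheses.
- **Outcomes {12}** says each secondary or exploratory outcome will be "reported as mean change within groups at week 8 from to baseline and compared between groups at each follow-up visit". Within-group change and between-group comparison stand side by side.
- **Statistical method outcomes {20a}, CDAI**: "Changes in score from baseline between groups will be compared within groups using two-sided, unpaired" t-tests, with change from baseline to closeout as the main outcome. Paired within-group t-tests are added. The non-parametric fallback is a rank-sum "test of mean values between groups will be used if data are non-normally distributed".
- **Statistical method outcomes {20a}, biomarkers** (cytokines, permeability, endotoxaemia, bile acids, platelets): effect sizes are compared qualitatively with phase I, the study is said to be powered for d = 1.2 between groups, and d > 0.5 counts as evidence of a possible effect. Significance testing is exploratory and limited to unpaired "tests between XN treatment groups".

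**The concern.** Three different comparisons can be read out of these sections: XN versus placebo in this trial, change within the XN arm, and XN in patients versus XN in healthy adults. Only the first isolates the effect of XN on Crohn's disease.

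Patients are selected on a CDAI above 150. Some of them are above the cut-off on a temporarily high score and will fall back without treatment, and placebo response adds to that. A within-arm test attributes all of this to XN. The healthy phase I cohort has no Crohn's activity to improve, so it cannot show whether XN improves it.

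At stake is what a reader may conclude from a small trial. Two analysts could run different tests, reach different conclusions on CDAI or TNF-α, and both cite the protocol. The d > 0.5 rule adds to this: because its contrast is not named, it could be applied to a within-arm or cross-trial change.

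**Working it through.** **1. What the planning figure implies.** Inputs: d = 1.2 between groups ({20a}), and 12 per group, 80% power and α = 0.05 (Sample size {14}). For a two-sided two-sample t-test the noncentrality is 1.2 × √(12/2) = 2.94 on 22 degrees of freedom, giving power of 80.2%. The n needed for 80% is 11.94, so 12 per arm. With 25% attrition, 24 / (1 − 0.25) = 32, as stated. The figure reproduces as a two-group contrast at the size of this trial's own arms, so the design was evidently sized for XN versus placebo.

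**2. Sections side by side.**

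- Pointing to placebo: the between-group half of the Outcomes {12} sentence; the unpaired test and rank-sum fallback for CDAI; d = 1.2 between groups; and Methods for additional analyses {20b}, which would adjust for CDAI if the groups differ at baseline.
- Pointing elsewhere: the comparator sentence in Hypotheses; the within-group half of Outcomes {12}; the paired CDAI tests; and the biomarker test restriction, which names XN groups in the plural where there is one.
- Undecided: the CDAI sentence, which says a between-group change is compared within groups, and the d > 0.5 threshold.

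No sentence ranks these or says which contrast decides.

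**3. Size of the within-arm problem for CDAI.** The protocol gives no CDAI mean, SD or reliability, so these are assumed: screened-population mean μ = 150 to 200, SD σ = 80, test-retest correlation r = 0.6 to 0.8, bivariate normal scores, entry at >150, and no drug or placebo effect.

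With a = (150 − μ)/σ and λ = φ(a)/[1 − Φ(a)]:

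- mean fall = (1 − r) σ λ
- SD of change = σ √[(1 − r)²(1 + aλ − λ²) + 1 − r²]

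*Upper end, μ = 150, r = 0.6:* a = 0 and λ = 0.798. Mean fall = 0.4 × 80 × 0.798 = 25.5 points. SD = 80 × √(0.16 × 0.363 + 0.64) = 66.8. Standardised change = 25.5/66.8 = 0.38.

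*Lower end, μ = 200, r = 0.8:* a = −0.625 and λ = 0.447. Mean fall = 0.2 × 80 × 0.447 = 7.2 points. SD = 80 × √(0.04 × 0.521 + 0.36) = 49.4. Standardised change = 7.2/49.4 = 0.145.

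The two-sided paired t-test at n = 12 (noncentrality = standardised change × √12, 11 degrees of freedom) is then significant in about 23% and 7% of trials, against a nominal 5%. In the XN-minus-placebo difference the same expected fall occurs in both arms and cancels, so the rate stays at 5%.

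This covers CDAI only. Biomarkers are not an entry criterion, so regression to the mean affects them only as far as they correlate with CDAI. Placebo response and natural course still apply to them.

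**The case against.** The strongest reply is that the protocol does plan the placebo comparison, several times over: twice in Outcomes {12}, in the CDAI tests, in the d = 1.2 statement and in the conditional baseline adjustment. That is correct. A reader might infer from the Hypotheses section that efficacy will be judged against phase I *instead of* placebo. The document as a whole does not support this.

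A reader might also infer from the biomarker test restriction that a formal t-test of phase II XN against phase I XN is planned. That is not supported either. The same paragraph describes the cross-trial comparison as qualitative, so the restriction is most naturally loose wording for this trial's two arms.

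It can further be said that the phase I reference was meant only for the metabolite profile, the one item in that sentence that mentions healthy adults, and that comparing effects between populations is a legitimate descriptive aim, the more so as phase I was itself placebo-controlled (Abstract). Both points are fair. They support keeping the phase I comparison as description. They do not repair the sentence, whose plain antecedent includes disease activity and inflammation.

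Finally, these outcomes are called exploratory and preliminary, and the trial's primary aim is safety. This lowers the severity. It does not settle which contrast an exploratory claim of effect rests on.

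**Conclusion.** The point holds as an internal contradiction. The placebo contrast is planned but is not fixed as the deciding one, and the most explicit comparator sentence and the biomarker test restriction both point away from it when read literally.

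The size can be illustrated only for the paired CDAI test: about 7% to 23% false positives at n = 12, under the assumed mean, SD and reliability and with no placebo response. Any placebo response in the direction of improvement would raise these rates. No planned sample size or power figure is affected.

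Severity is modest: the outcomes are exploratory, but the correction is easy and decides how any claim of benefit may be read.

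**What to change.** - **Hypotheses:** state that the hypotheses on clinical activity and inflammatory biomarkers are judged against this trial's placebo arm. Keep phase I as the reference for the comparison with healthy adults.
- **Outcomes {12}:** define the endpoint of each CDAI and biomarker outcome as the XN-minus-placebo difference in change from baseline to week 8, with earlier visits as supporting information.
- **Statistical method outcomes {20a}, CDAI:** rewrite the garbled sentence so that change from baseline is compared between the XN and placebo groups. Report within-arm change with estimates and confidence intervals, without paired tests.
- **Statistical method outcomes {20a}, biomarkers:** replace "tests between XN treatment groups" with *tests between the XN and placebo groups*, and state that the d > 0.5 threshold applies to that same difference.
- **Any phase I comparison:** report it descriptively, without p-values.

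The cost is wording in four places and the loss of within-arm p-values. No new data, visits or participants are needed, and power for d = 1.2 at 12 per arm stays at 80.2%. The change should be made while allocation is still masked.
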